### Data collection, management, and analysis

The information obtained will be recorded in a Microsoft Office Excel 2010 database and exported for statistical analysis to the Statistical Software for Data Science (Stata) V.16. A description of the outcome variables and the population characteristics will be carried out to display the statistical behavior of these variables. Qualitative variables will be presented as frequencies and percentages, while quantitative variables will undergo the Kolmogorov-Smirnov test to determine whether their behavior is parametric or non-parametric.

If parametricity is confirmed, a Levene’s test for equality of variances will be conducted. Once parametricity is established, a paired t-test will be performed to compare pre- and post-intervention results for each group. For non-parametric behavior, the Wilcoxon test will be used, and variables will be presented as medians and interquartile ranges. Additionally, comparisons of the three experimental groups will be made at the start and end of the intervention. If the variables exhibit parametric behavior, a one-way ANOVA test will be used, followed by post hoc tests. For parametric variables with equal variances, the Tukey test will be applied (adjusting for unbalanced groups with Dunnett’s T3 test). If equal variances are not assumed, Dunnett’s T3 test will be used. For non-parametric variables, the Kruskal-Wallis test will be employed. A significance level of 95% will be considered, with a p-value < 0.05 regarded as statistically significant.

An analysis of covariance (ANCOVA) regression model will be used to evaluate the main effect of the outcome variable among the three experimental groups, adjusting for age, sex, and other potential confounding factors (those statistically significant at the 5% level).

A logistic regression model will be considered to analyze a binary outcome (e.g., adherence to recommendations provided through telephone follow-up), utilizing Akaike’s information criterion to select the best model based on its bias and variance.

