### Sample

The population will include patients with a diagnosis of HF who will be admitted to a cardiac rehabilitation program in the city of Santiago de Cali, Colombia. It should be noted that this study aims to compare quantitative variables. Studies that compare means use the standard deviation as a measure of variation, so the variable of interest will be the distance covered in meters in the 6-minute walk test (6MWT).

The hypothesis of this study proposes that the group receiving telerehabilitation, telephone follow-up, and education will achieve better results in patients’ aerobic capacity, compared to the other experimental groups.

There are no studies with similar characteristics with telephone follow-up to obtain a walking distance equal to that of the telerehabilitation group. This is because the groups are homogeneous at the beginning of the intervention but heterogeneous at the end of the intervention program; 378.5 ± 96.9 for the conventional outpatient cardiac rehabilitation group and 432 ± 83 for cardiac telerehabilitation).

In turn, 95% confidence is estimated, error α: 5% (0.05), error β: 20% (0.20), power: 1-β: 80%, giving n = 46 participants for each experimental group, which is increased by 12% for possible problems in the measurements or dropouts of the study participants, so that n = 52 will be required and a total of 156 patients with HF per experimental group at the end of the study.

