### Intervention

Prior to enrollment, patients will be seen in person for assessment of anthropometric data (height, weight, percent fat, water, muscle mass, and abdominal circumference), laboratory tests (total cholesterol, HDL, LDL, triglycerides, blood glucose, BUN), functional aerobic capacity (6MWT and sit-to-stand test), depression and anxiety questionnaires (HADS, Patient Health Questionnaire 9, PHQ-9), functional capacity (Duke Activity Status Index (DASI)), and health-related quality of life (HRQoL) Minnesota Living with Questionnaire MLFHQ [6]. These data will be collected again at the end of the 12-week intervention program.

The following is a detailed description of each intervention to be performed in this study, the assignment of the intervention according to the experimental group (Table 1), and the exercise prescription for each group (Table 2).

**Table 1 pone.0327366.t001:** Interventions assigned to each experimental group.

Arms	Intervention			
	Conventional rehabilitation	Education	Telerehabilitation	Telephone follow-up
Experimental Group 1		**x**	**x**	**x**
Experimental Group 2	**x**	**x**		
Experimental Group 3		**x**	**x**	

**Table 2 pone.0327366.t002:** Exercise prescription.

Arms	Exercise prescription

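### Baseline 6MWT is measured but not fixed as a covariate, and the plan does not say whether the unadjusted test or the ANCOVA decides; fixing both costs no data and gains power

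*Protocol article*

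**What the plan says.** The Sample section makes walking distance the sizing outcome: "the variable of interest will be the distance covered in meters in the 6-minute walk test (6MWT". Its hypothesis is that the arm with telerehabilitation, education and telephone calls (Group 1) does better than the other two arms. The Intervention section measures 6MWT before enrolment and adds: "These data will be collected again at the end of the 12-week intervention program".

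The section on data collection, management and analysis then sets out four layers:

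- Quantitative variables "undergo the Kolmogorov-Smirnov test to determine whether their behavior is parametric or non-parametric".
- Paired t or Wilcoxon tests compare pre and post values within each arm.
- Between arms, "comparisons of the three experimental groups will be made at the start and end of the intervention". The parametric branch is one-way ANOVA with Tukey or Dunnett's T3 post hoc tests. For the other branch the text is: "For non-parametric variables, the Kruskal-Wallis test will be employed". No pairwise procedure follows.
- An ANCOVA assesses the main effect across the three arms, "adjusting for age, sex, and other potential confounding factors (those statistically significant at the 5% level").

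The section does not rank the ANOVA/Kruskal-Wallis route against the ANCOVA.

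**The concern.** Baseline 6MWT is likely to be among the strongest predictors of 12-week 6MWT. The unadjusted comparison leaves it out, so a chance difference between arms at the start passes into the estimated effect, and variance that could be explained stays in the error term. The ANCOVA could repair this, but baseline distance is not named in it. Entry is left to a significance rule that does not say what is being tested.

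The hypothesis is also pairwise. If the pre-test sends 6MWT to the rank branch, that branch as written gives one three-group result, which cannot show which arm is better. The ANCOVA could supply contrasts, but the plan does not say that it decides. Two between-arm analyses may therefore disagree with no rule to choose between them.

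**Working it through.** **Inputs from the Sample section.** End-of-programme distances: "378.5 ± 96.9 for the conventional outpatient cardiac rehabilitation group and 432 ± 83 for cardiac telerehabilitation". Error rates: "error α: 5% (0.05), error β: 20% (0.20), power: 1-β: 80" per cent. There are 46 per arm before the dropout allowance.

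**Reproducing the plan's own figure.** Difference = 432 − 378.5 = 53.5 m. Root-mean-square SD = √[(96.9² + 83²)/2] = 90.2 m. Normal approximation, two-sided 5%, 80% power: n = 2 × [90.2 × (1.960 + 0.842)/53.5]² = 44.6, so 45. With the noncentral t distribution, power is 79.4% at 45 and 80.3% at 46, so 46 reproduces. The sizing is therefore a two-arm, two-sided comparison of end values, with no baseline adjustment and no multiplicity allowance.

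**Effect of adjusting for baseline.** If r is the correlation between baseline and 12-week 6MWT, the residual SD is 90.2 × √(1 − r²) and the standard error of a contrast at 46 per arm is that SD × √(2/46). The protocol does not give r; 0.3 to 0.8 is an assumed range. The degrees of freedom lost to covariates are ignored. The Tukey column uses the three-arm critical value 2.37 (135 df).

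| r (assumed) | Residual SD (m) | SE (m) | Power, two-sided 5% | Power, Tukey | Difference detectable at 80% power, two-sided 5% (m) |
|---|---|---|---|---|---|
| end values only | 90.2 | 18.8 | 80.3% | 68.2% | 52.7 |
| 0.3 | 86.1 | 17.9 | 83.9% | 72.9% | 50.3 |
| 0.5 | 78.1 | 16.3 | 90.1% | 81.8% | 45.6 |
| 0.7 | 64.4 | 13.4 | 97.6% | 94.5% | 37.6 |
| 0.8 | 54.1 | 11.3 | 99.7% | 99.1% | 31.6 |

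The comparison that may need this most is Group 1 vs Group 3, for which the protocol gives no expected difference. At an assumed 30 m, power (two-sided 5%) is 35% on end values, against 45%, 60% and 75% at r = 0.5, 0.7 and 0.8.

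**Does the ANCOVA's 5% rule bring baseline in?** This was simulated with three arms of 46, both telerehabilitation arms 53.5 m above the conventional arm, r = 0.5, 0.7 and 0.8, and 3,000 runs each.

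- Selection by association with the outcome: baseline was selected in 100% of runs and the full gain was kept (90.1%, 97.6%, 99.7%).
- Selection by imbalance between arms: baseline was selected in about 5% of runs (4.6%, 5.1%, 4.9%), and power stayed at 82% to 83%.

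The text supports either reading. Its reference to confounding points towards the second.

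**What the rank branch can show.** In the same simulation Groups 1 and 3 were identical, yet Kruskal-Wallis was significant in about 82% of runs. A significant result there does not show that Group 1 beats Group 3.

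**The case against.** The best defence is the ANCOVA. A reader might infer that the plan ignores baseline 6MWT, or that a failed normality test leaves only Kruskal-Wallis and the hypothesis untested. The text does not support either. The ANCOVA is not conditional on the pre-test, its 5% rule can admit baseline distance, and arm contrasts can be taken from it. The unadjusted end-value comparison is also unbiased under randomisation, and the trial was sized on it. The size of the loss rests on a correlation that the protocol does not give; at r = 0.3 the gain is under 4 points. All of this stands and limits the point to efficiency and clarity.

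Two side issues carry little weight. One might argue that the within-arm paired tests will produce conflicting verdicts. With an identical 20 m gain in every arm and an SD of change of 60 m (both assumed), each paired test has about 60% power and the arms disagree in 1 − 0.6³ − 0.4³ = 72% of trials. That is close to the maximum of 75%; the figure falls to 24% at a 30 m gain and 2% at 40 m. The plan also does not say that arms will be judged by comparing within-arm p-values. Dunnett's T3 is meant for unequal variances rather than unequal group sizes, but the critical value is about 2.43 against Tukey's 2.37, so the effect is trivial.

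It may also be said that covariate lists and post hoc steps belong in an SAP that is not shown. That is fair for mere silence, and the missing pairwise step should not carry the point alone. But the article does fix a normality gate and a significance-based covariate rule, and it sets two between-arm analyses side by side without ranking them.

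**Conclusion.** The point holds as a free improvement that should be made, not as a fatal flaw. Baseline 6MWT is collected but not fixed in any between-arm analysis. Its entry into the ANCOVA turns on an ambiguous, data-driven rule, and no analysis is named as decisive. At 46 per arm and 53.5 m, fixing it raises power from 80% to between 84% and 99.7%, or from 68% to between 73% and 99% under the plan's own Tukey test. Both ranges rest on an assumed r of 0.3 to 0.8. The gain is measured against the end-value comparison; if the ANCOVA decides and its rule means association with the outcome, most of it is already secured. Adjustment lowers the error variance at any non-zero correlation; only the amount depends on r.

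**What to change.** Name one primary analysis that holds whatever the normality test shows: ANCOVA of 12-week 6MWT on arm, baseline 6MWT, age and sex, with no covariates selected by significance. Take the Group 1 vs 2 and Group 1 vs 3 contrasts from that model with 95% confidence intervals, under a stated multiplicity rule. As a guide to its cost, Bonferroni over the two contrasts gives 71.3% power per contrast on end values at 53.5 m, and 75.7%, 84.0%, 95.4% and 99.2% with baseline at r = 0.3, 0.5, 0.7 and 0.8. Analyse continuous secondary outcomes the same way, each with its own baseline. Keep within-arm changes as description. If a rank test is retained, make it a sensitivity analysis and name its pairwise procedure.

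The cost is wording in the analysis plan, settled before the outcome data are analysed. No new data are needed. By the article's dates recruitment closed on 30/01/2025, so adjustment is a way to gain precision without further patients.

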Regarding the frequency and duration of the telerehabilitation program, significant differences in the duration of the program in weeks are observed among the different studies, with periods ranging from 8 to 18 weeks, according to the literature on the subject [8,19,20,25,26]. This study defines a 12-week intervention program with sessions scheduled three times per week. This approach is similar to previous clinical trials, which suggest a frequency of intervention between 3 and 5 times per week [8,19,20,22,24]; moreover, it is consistent with the cardiac rehabilitation sessions generally prescribed in Colombia [6].

Concerning exercise prescription, the session is divided into three main phases: warm-up, core training, and cool-down. Concerning intensity, a range of 50% to 70% of HRmax and a value of 11–13/20 according to the conventional Borg scale are established. These results are congruent with those reported in other telerehabilitation studies for patients with HF [8,23–25] and reflect appropriate exercise prescriptions for patients and replication of the study. In addition, to track and monitor the prescription in this study, patients are given an FT4 fleece belt and a digital blood pressure monitor, similar to some studies in which patients were given digital devices to monitor vital signs [9,10,12,17,18] or taught how to take their vital signs [14].

Mobile technology in healthcare allows assessment, measurement, intervention, and remote follow-up synchronously or asynchronously, enabling its application in CR, improving cost-effectiveness, time and interaction with patients, and treatment adherence [27]. Studies involving telephone follow-up have generally been conducted in conventional outpatient rehabilitation programs or at home [28–30], This study aims to provide further insights into cardiac telerehabilitation programs for patients with HF. It demonstrates positive effects on quality of life, reductions in stress and depression levels, and improvements in treatment adherence, thereby facilitating the achievement of therapeutic goals, similar to what was presented in other studies [27,31].

Some limitations of this study include the potential dropout of patients from any of the three groups due to personal or health-related factors, especially in the conventional rehabilitation group, where patients are required to travel to the rehabilitation clinic.

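### The post hoc rule uses Dunnett's T3, an unequal-variance procedure, to handle unequal group sizes, and leaves the ordinary one-way ANOVA in place when variances differ; the effect is modest.

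*Protocol article*

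**What the plan says.** All of the rule is in the protocol article, section Data collection, management, and analysis.

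- Variance check: "If parametricity is confirmed, a Levene’s test for equality of variances will be conducted".
- Overall test: "If the variables exhibit parametric behavior, a one-way ANOVA test will be used, followed by post hoc tests". No Welch or Brown-Forsythe version is named.
- Post hoc test, equal variances: "For parametric variables with equal variances, the Tukey test will be applied (adjusting for unbalanced groups with Dunnett’s T3 test".
- Post hoc test, unequal variances: "If equal variances are not assumed, Dunnett’s T3 test will be used".
- Level: "with a p-value < 0.05 regarded as statistically significant".
- Separately: "An analysis of covariance (ANCOVA) regression model will be used to evaluate the main effect of the outcome variable among the three experimental groups".

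Two other sections bear on the size of the effect. Sample gives the planning figures for the 6-minute walk distance: "378.5 ± 96.9 for the conventional outpatient cardiac rehabilitation group and 432 ± 83 for cardiac telerehabilitation". Discussion expects dropout in any arm, but "especially in the conventional rehabilitation group, where patients are required to travel to the rehabilitation clinic".

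**The concern.** The rule has two faults.

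First, unequal group sizes do not call for T3. With equal variances, Tukey-Kramer allows for unequal n and still pools the variance over all three arms. T3 uses only the two arms being compared and has a larger critical value. The section sets no threshold for calling groups unbalanced. Read literally, almost any dropout would move the analysis to T3, and Levene's result would then hardly affect the choice of post hoc test. At stake is some power in the between-arm comparisons.

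Second, when Levene's test points to unequal variances, only the post hoc test changes. The overall F test assumes equal variances and is liberal when the smaller arm is the more variable one. The protocol's figures lean that way: the conventional arm has the larger planning SD and is singled out for dropout.

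**Working it through.** **Inputs.** From Sample: means 378.5 and 432, SDs 96.9 and 83, 46 per group, raised by 12% to 52, alpha 0.05, power 80%. Assumed, because the article does not give them: two-sided tests, normal data, final group sizes, SD 83 in both telerehabilitation arms in the unequal-variance runs, and a 53.5 m difference for Group 1 v conventional. Group sizes are written telerehabilitation/conventional/telerehabilitation. Simulated figures rest on 60,000 to 100,000 trials per setting.

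**1. The protocol's own sample size.** Difference = 432 − 378.5 = 53.5. SD = √((96.9² + 83²)/2) = 90.2. n = 2(1.96 + 0.842)² × 90.2²/53.5² = 44.6, so 45; the t-based solution is 45.6, so 46. Then 46 × 1.12 = 51.5, so 52. The stated figures reproduce, as a single unadjusted two-group comparison.

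**2. How often groups end exactly equal.** With independent Binomial(52, 0.12) losses in three arms, the chance that all three are equal is Σ P(K = k)³ = 0.017.

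**3. Power with equal variances (SD 90.2).** The Tukey-Kramer critical value is q(0.05; 3, N − 3)/√2 = 2.37. The T3 value (studentised maximum modulus, three comparisons, Welch df near 90) is 2.43.

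- 46 v 44: SE = 90.2 × √(1/46 + 1/44) = 19.02, and 53.5/19.02 = 2.81. Power is Φ(2.81 − 2.37) = 67% for Tukey-Kramer and Φ(2.81 − 2.43) = 65% for T3.
- 46 v 36: SE = 90.2 × √(1/46 + 1/36) = 20.08, and 53.5/20.08 = 2.66. Power is about 62% and 59%.

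Simulation agrees: 67.1% v 64.6% at 46/44/47, and 61.7% v 59.1% at 46/36/46. With other sizes: 71.1% v 68.9% at 52/46/52, 58.6% v 55.4% at 52/30/52, and 45.3% v 41.2% at the extreme 52/20/52. In unbalanced groups with equal variances, Tukey-Kramer's family-wise error is 4.7-5.1%, so it needs no replacement there.

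**4. Level of the overall F with unequal variances.** Under equal means, the expected between-group mean square is Σ(1 − nᵢ/N)σᵢ²/2 and the expected error mean square is Σ(nᵢ − 1)σᵢ²/(N − 3). With SDs 83/96.9/83:

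- 46/46/46: 7,722.5/7,722.5 = 1.00.
- 46/36/46: 7,787.7/7,589.2 = 1.03.
- 52/20/52: 7,937.6/7,281.7 = 1.09.

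So F drifts upwards as the more variable arm shrinks. Simulated rejection rates at nominal 5%:

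| SDs | Sizes | Ordinary F | Welch | T3, family-wise |
|---|---|---|---|---|
| 83/96.9/83 | 46/46/46 | 5.1% | 5.1% | 4.5% |
| 83/96.9/83 | 52/46/52 | 5.3% | 5.1% | 4.6% |
| 83/96.9/83 | 52/40/52 | 5.5% | 5.0% | 4.4% |
| 83/96.9/83 | 52/30/52 | 5.8% | 4.9% | 4.4% |
| 83/96.9/83 | 52/20/52 | 6.6% | 5.2% | 4.5% |
| 83/96.9/83 | 30/52/52 | 4.7% | 5.0% | 4.5% |
| ratio 1.5 (assumed) | 52/40/52 | 6.7% | 5.1% | 4.5% |
| ratio 2 (assumed) | 52/30/52 | 10.8% | 5.0% | 4.2% |

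At 46/36/46 with the protocol's SDs the F is at about 5.3%.

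**5. Does Tukey-Kramer after Levene's test have a cost?** At the planning SDs, Levene's test rejects in only about 12-16% of trials. Tukey-Kramer, replaced by T3 only when Levene rejects, then has family-wise error of about 5.2% at 46/36/46 and about 6% at 52/21/52. T3 used throughout stays near 4.4%.

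**The case against.** The strongest defence is that T3 for unbalanced groups is a cautious choice. If the smaller arm really is more variable and Levene's test misses it, pooled Tukey-Kramer is slightly liberal and T3 is not. Step 5 bears this out, so it would be wrong to say that T3 brings no gain in validity. That is an argument about unequal variances, however, and the sentence in question applies where variances have been taken as equal and gives imbalance as the reason.

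A second defence is that the rule has limited reach. ANCOVA carries the main effect, and non-parametric variables go to Kruskal-Wallis. This stands. A reader might infer that power is lost on every outcome; the protocol does not support that.

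A third is that the article is merely silent on Welch's version, which an analysis plan could supply. This stands only in part. The section does say what changes when equal variances are not assumed, and that is the post hoc test alone.

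A reader might also infer that the trial's 5% level is lost. The figures do not support it. The trial's hypothesis concerns one arm against the others, and the T3 comparisons that would test it in this branch stay below 5%. Only the overall F drifts, and if another arm is the smaller one it is slightly conservative. Values of 6% or more at the protocol's SDs need something like 29 conventional patients left out of 52, a loss of 23/52 = 44% against the planned 12%. The Discussion gives no dropout figure by arm, and the Sample section does not predict unequal variances.

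**Conclusion.** The point holds as a method error of modest size in a stated rule. T3 is assigned to the wrong problem, and the overall test is not matched to the variance finding that the plan itself tests for. In the unadjusted comparisons the cost is about 2 to 3 points of power when variances are equal. When the conventional arm is both smaller and more variable, the overall F is at about 5.3-5.5% at the protocol's SDs and plausible dropout. Clearer inflation requires heavy imbalance or an SD ratio above the planning value of 96.9/83 = 1.17. These figures assume normal data, two-sided tests and the group sizes shown. The preliminary Kolmogorov-Smirnov step was not simulated, and Levene's step enters only in the last calculation.

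**What to change.** Delete the parenthesis that assigns T3 to unbalanced groups, and write: *When equal variances are assumed, one-way ANOVA with Tukey-Kramer pairwise comparisons, whatever the group sizes. When they are not, Welch's ANOVA with Dunnett's T3 (or Games-Howell).*

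This has a small downside. Because Levene's test has little power at the planning SD ratio, Tukey-Kramer can run slightly above 5% if the smaller arm is the more variable one. If strict error control is preferred, use Welch's ANOVA with T3 or Games-Howell throughout, accept the 2 to 3 points of power, and state that possible unequal variances, not imbalance, are the reason.

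Either version costs two sentences of analysis text, needs no patients or new data, and should be settled before the data are analysed.

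### The arm difference in the outcome is tested twice at p<0.05, by ANOVA/Kruskal-Wallis and by ANCOVA, with neither named as deciding; if either may decide, the 5% error rises to between about 5.5% and 9%

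*Protocol article*

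**What the plan says.** All of this is in the protocol article. Under Sample, the 6-minute walk distance is the variable of interest, and the size calculation uses "error α: 5% (0.05), error β: 20% (0.20), power: 1-β: 80" percent.

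Under Data collection, management, and analysis, two between-arm tests are described:

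- **Unadjusted.** After the distribution checks and the within-group tests, "comparisons of the three experimental groups will be made at the start and end of the intervention". The method is one-way ANOVA with post hoc tests, or Kruskal-Wallis if the variable is judged non-parametric.
- **Adjusted.** In a separate paragraph, "An analysis of covariance (ANCOVA) regression model will be used to evaluate the main effect of the outcome variable among the three experimental groups". Age and sex are named as covariates. Other possible confounders enter if they are significant at 5%.

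One decision rule is given: "A significance level of 95% will be considered, with a p-value < 0.05 regarded as statistically significant". The section ranks neither test as primary, confirmatory, supportive or sensitivity, and it does not divide the 5% between them.

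**The concern.** Both tests ask whether the arms differ on the same end-of-treatment outcome. With one threshold and no order between them, a report could call the trial positive if either test falls below 0.05, while the design budgets 5% for a single test.

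The better the covariates predict the outcome, the less the two tests agree, so the second test then offers more of an extra chance. A reader of the results could not tell whether a claimed effect came from the planned test or from the more favourable of two.

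**Working it through.** **Reproducing the plan's own figure.** The inputs come from the Sample section: "378.5 ± 96.9 for the conventional outpatient cardiac rehabilitation group and 432 ± 83 for cardiac telerehabilitation", alpha 0.05 (two-sided assumed), power 80%.

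- Difference: 432 − 378.5 = 53.5 m.
- Pooled SD: √((96.9² + 83²)/2) = 90.2 m.
- Normal approximation: n = 2 × (90.2 × (1.960 + 0.842)/53.5)² = 44.6 per arm. The t-based version gives 45.6, which rounds up to the stated 46.
- Allowance: 46 × 1.12 = 51.5, so 52 per arm and 3 × 52 = 156 in total.

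The stated size is therefore reproduced for one comparison tested once at 5%.

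**Error with two tests.** Trials were simulated with no arm difference, three arms of 52 and 20,000 runs per setting. Each data set was tested by ANOVA (or Kruskal-Wallis) and by ANCOVA with three fixed covariates, each at 0.05. A false positive was counted if either test rejected. R², the share of outcome variance explained by the covariates, is not in the article and was varied:

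| R² (assumed) | ANOVA or ANCOVA | Kruskal-Wallis or ANCOVA |
|---|---|---|
| 0 | 5.4% | 6.0% |
| 0.05 | 6.5% | 6.6% |
| 0.10 | 6.5% | 6.6% |
| 0.20 | 7.1% | 7.2% |
| 0.50 | 8.2% | 8.3% |
| 0.70 | 8.9% | 8.9% |
| 0.80 | 9.5% | 9.3% |

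Each test alone stayed between 4.8% and 5.4%. Two independent tests would give 1 − 0.95² = 9.75%, which the table approaches as R² grows. The simulation error of an entry near 8% is about √(0.08 × 0.92/20,000) = 0.2 percentage points.

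**Check at 46 per arm.** By correlation between covariate and outcome, the either-test error was 6.5%, 7.2%, 8.2% and 8.7% at 0.3, 0.5, 0.7 and 0.8. It was about 5.3% with useless covariates. A single covariate's R² is the square of its correlation, so 0.7–0.8 means R² of 0.49–0.64.

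**Covariates chosen by 5% significance.** The article does not say what the candidates are tested against, so two rules were simulated (10,000 runs each, 52 per arm, R² of 0.05, 0.2, 0.5 and 0.7):

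- Selected by association with the outcome: either-test error 6.3%, 7.6%, 8.5% and 9.1%.
- Selected by imbalance between arms: about 6.0% throughout. The ANCOVA itself then rejected too rarely, at 3.5% and 3.3% for R² of 0.5 and 0.7.

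**How often the tests disagree when there is an effect.** If both telerehabilitation arms gain 53.5 m with SD about 90 m (an assumption about the third arm), one test is significant and the other is not in roughly 7% of trials at correlation 0.3 and 12% at 0.5.

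**The case against.** The strongest reply is that the roles are implied. The unadjusted comparison sits among routine descriptive and within-group tests and covers quantitative variables in general. The ANCOVA has its own paragraph and refers to a single outcome variable. Reporting unadjusted and adjusted results together is ordinary practice, and an analysis plan that is not shown may name the deciding test.

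Part of this stands. The article calls neither test confirmatory and nowhere says that success on either would establish efficacy. A reader might infer that the true error of this trial is 6–9%, but the text does not support that as a fact. The excess arises only if either result may carry the claim. Its upper end also needs strong covariates, and the article names only age and sex. If those explained about 10% of the variance (assumed), the figure would be about 6.5%.

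The reply does not remove the point. The ANCOVA's description gives its purpose but does not demote the ANOVA. The ANOVA falls under the same significance rule and is the only one of the two with stated post hoc procedures, so pairwise claims for the trial's hypothesis would naturally come from it. What the article fixes is two tests under one rule, with covariates chosen from the data.

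A reader might also infer that choosing covariates by significance adds to the either-test error. The simulations do not show this. Selection by association gave 6.3–9.1%, against 6.5–8.9% for fixed covariates over the same R² range, and selection by imbalance gave less.

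**Conclusion.** The point holds in conditional form. The article plans two tests of one arm difference at p<0.05 and does not say which decides. If either may support a claim, the error on that outcome is about 5.5–6.5% with weak covariates and about 8–9% with correlations of 0.7–0.8. If one test is named, it is about 5%.

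The figures rest on assumed correlations, a null effect in all arms and complete data. They cover only the duplicated three-arm test on one outcome. They exclude the secondary outcomes, the within-group tests and the choice between ANOVA and Kruskal-Wallis after a normality test.

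The case for fixing the covariates does not depend on added error in the either-test rate. A set chosen by significance leaves the adjusted analysis undefined until the data are seen, and under one reading of the rule it makes that analysis conservative.

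**What to change.** For 6-minute walk distance, name the ANCOVA as the single deciding analysis. Fix its covariates in advance: age, sex and a short list of variables measured before randomisation, for which baseline walk distance is the obvious candidate. Drop selection by 5% significance. Label the end-of-treatment ANOVA or Kruskal-Wallis comparison as supportive only.

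This takes about one sentence and changes neither the sample size nor the conduct of the trial. It should be written before outcomes are compared by arm. The article gives recruitment as ended on 30/01/2025 and completion as planned for 20/06/2025, but does not say whether that comparison has been made.

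There are two costs. A significant unadjusted test alone can no longer support a claim of effect. The pairwise comparisons, now described only for the ANOVA, would also have to come from the ANCOVA model.
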